### 3.3. Cross-Sectional Surveys

#### 3.3.1. Overview

There will be four cross-sectional surveys during the study period;

- Pilot cross sectional survey– February - March 2011
- Baseline cross sectional survey– June 2011

Intervention: Withdrawal of spraying in one arm September 2011

- Post Intervention Survey A– February - March 2012, 5 months after the intervention
- Post Intervention Survey B– June 2012, 8 months after the intervention

Each survey will include two components; 1) a household component and 2) a parasitological component. The household component will be conducted in 100 houses selected at random from the core sampling area (figure 7). A questionnaire will be administered to obtain information on possible

risk factors for malaria and a maximum of two children from eligible household will be selected. Children will be sent to a central point the following day for the parasitological testing.

[figure not shown]

**Figure 7:** Detailed map of the survey area of one cluster. Blue flag represent the houses that have been selected for the survey and need to be visited. Green dot indicate the other houses.

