### **3.6. Interventions**

During stage 2 in February 2011 an IRS round has been completed in Muleba district including all the selected clusters of our survey area. Another round is planned in September-October 2011 and will target only half of the cluster randomly selected to the IRS plus LLINs study arm.

In March 2011, a LLIN distribution campaign supported by Mennonite Economic Development Associates (MEDA) and funded by Global Fund is scheduled and aims to reach universal coverage. However preliminary information shows a really low bed-net usage, this suggests that an intensive Information Education Communication (IEC) campaign is required to get high usage of LLINs.

Additional net will probably need to be secured to top up the universal coverage campaign and insure that every sleeping place is covered by a LLIN in the survey area. The bed-net coverage given by the pilot survey will help us to estimate the quantity of LLINs needed to reach universal coverage and identify if additional LLINs are required after the Global Fund LLIN distribution of March. LLIN integrity will be assessed during the baseline year (where already used) and at the end of the study period using WHO recommended assessment of durability. The association between integrity and protectiveness will be analysed.

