#### 4. Work Plan

The trial will run for 2 years as per the detailed work plan and schedule. A comprehensive work plan and project schedule is outlined in this section (and is divided in 4 stages).

1. Stage 1: **The preparation** (Sept-Dec 2010) during which the project was established in Kagera region. A project manager ([name]) was recruited and based in Muleba. A project office was secured in Muleba as a headquarters for field activities, administration, reference laboratory and entomology. Project staff were recruited and trained. Coordination with district health authorities was achieved.

The main technical activity during the first quarter was the mapping of the trial area consisting of more than 100 villages in which the study will be conducted. Each house in each hamlet was geo-referenced to facilitate the allocation of interventions and the sampling of households for cross sectional surveys and entomological surveillance. A detailed quarterly report covering this phase has been submitted.

2. Stage 2: **The pilot** (Jan to March 2011). Following the mapping conducted during the preparatory phases, 51 clusters comprising of 1 up to 3 villages were identified, and 100 houses randomly selected per cluster. A pilot cross sectional parasite survey to evaluate prevalence in the study area is ongoing and started in February. Based on the prevalence data the final selection of study clusters will be made. An IRS round just finished before the beginning of the pilot cross sectional survey.
3. Stage 3: **The baseline** (April-Sept 2011). During this stage it is anticipate that a distribution campaign of LLINs will occur beginning April with the objective to reach universal coverage. A second cross sectional prevalence survey (June-July), entomological monitoring, a feasibility evaluation of acquiring incidence data from health facility integration will be also conducted. The laboratory will be fully set up, SOPs for the different techniques written and staff trained.
4. Stage 4: **The intervention**, (Sept 2011-Aug 2012) anticipates IRS in Sept-Oct 2011 in half the clusters and distribution of LLIN to top up the universal campaign and reach a coverage and usage of minimum 80% in all the cluster. It will depend on whether RTI is sprayed in Sept 2011 or February 2012. Cross sectional prevalence surveys in Feb-March and again in June-July, with entomological and incidence monitoring from Jan-July will also be conducted.

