| Timeline anticipates IRS in Sept-Oct 2011 in half of clusters (subject to change) and LLIN distribution to top up coverage in all clusters |                                                               |                                                                                                                                                                                                                                                                                                                                                                       |                                                                                 |

|                                                                                                                     |                                                            |                                                                                                                                                                                                                                                                                                                                                                                                                                                                                                                                                      |                                                 |
|---------------------------------------------------------------------------------------------------------------------|------------------------------------------------------------|------------------------------------------------------------------------------------------------------------------------------------------------------------------------------------------------------------------------------------------------------------------------------------------------------------------------------------------------------------------------------------------------------------------------------------------------------------------------------------------------------------------------------------------------------|-------------------------------------------------|

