| Sensitization                                                                                                       | Meeting with ward, village and hamlet leader        | 
 
The hamlet leader are informed about the purpose of the study
 
The hamlet leader are explained which one will get witch intervention
 
                                                                                                                                                                                                                                                                                                                                                       |                                                 |
| LLIN distribution top up
(MEDA/NMCP/LSHTM, KCMC, NIMR)                                                           |                                                            | 
 
Determination of net requirement by cluster
 
Planning distribution activities
 
Training for implementation
 
Distribution
 
Monitoring of coverage
 
                                                                                                                                                                                                                                                                                                                   | August 2011
Sept-Oct 2011                    |
| Cross-sectional post intervention survey
A
(100 children from ~100 households in each of ~30 clusters) | Questionnaires                                             | 
 
Completion of questionnaire survey in ~100houses within each of 30 clusters
 
Household census & risk factors data 
 
Socioeconomic data
 
Bednet usage; IRS and other insecticide use
 
 
 
% of children who slept under an ITN/LLIN on the previous night
 
% of households with evidence of IRS in September 2011, e.g. adult recall, IRS 
 
House structural data
 
 
 
 | Jan-Feb 2012

Feb-March 2012              |

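### If the arm A spray round moves to February 2012 and the printed survey months stand, Survey A falls about 0–2 months after it, and any non-inferiority comparison using that survey leans towards success

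*Protocol*

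**What the plan says.** Protocol sections 2.4, 3.3.1 and 3.6 place the arm A round in September or September-October 2011. The work plan (section 4, Stage 4) has the same expectation but then adds: "It will depend on whether RTI is sprayed in Sept 2011 or February 2012". The Stage IV table also marks the date as provisional: "Timeline anticipates IRS in Sept-Oct 2011 in half of clusters (subject to change".

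Section 3.3.1 fixes each post-intervention survey twice, by month and by interval. Survey A is "February - March 2012, 5 months after the intervention" and Survey B is "June 2012, 8 months after the intervention". Stage 4 repeats the months directly after the contingency, without adjustment: "Cross sectional prevalence surveys in Feb-March and again in June-July", "with entomological and incidence monitoring from Jan-July will also be conducted". Stage 4 ends in August 2012.

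The Stage IV table gives partly different dates. Survey A questionnaires are due in Jan-Feb 2012 and its blood tests in Feb-March. Survey B questionnaires are due in April-May and its children are surveyed in May-June.

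On spray history, section 3.6 reports that "in February 2011 an IRS round has been completed in Muleba district including all the selected clusters". Both arms receive nets.

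**The concern.** The arm A round is the only planned difference between the arms. Until it happens, both arms have the same February 2011 spraying and the same net campaign. A survey taken before the round, or just after it, will find the arms alike whether or not withdrawing IRS does harm.

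In a superiority trial that would cost power. In a non-inferiority trial, similarity is the success criterion, so the error runs towards declaring withdrawal acceptable. Section 3.3.3 lists the post-intervention surveys as the place where the arms are compared, and section 2.2 would use the result as reassurance that IRS can safely stop. The February branch is the protocol's own, and the plan does not say that the surveys move with the round.

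**Working it through.** **Inputs.** Arm A round: September 2011 (sections 2.4, 3.3.1), Sept-Oct 2011 (sections 3.6, 4) or February 2012 (section 4, Stage 4). Survey A: Feb-March 2012. Survey B: June (section 3.3.1), June-July (Stage 4 text), April-May or May-June (Stage IV table). Previous round in all clusters: February 2011 (section 3.6). Design figures: section 2.6 and Table 1.

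**Step 1: intervals in months, midpoint of the spray window to midpoint of the survey window.**

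| Arm A round | A: Feb-March | B: June | B: June-July | B: April-May (table) | B: May-June (table) |
|---|---|---|---|---|---|
| Sept-Oct 2011 | 5.0 | 8.5 | 9.0 | 7.0 | 8.0 |
| September 2011 | 5.5 | 9.0 | 9.5 | 7.5 | 8.5 |
| February 2012 | 0.5 | 4.0 | 4.5 | 2.5 | 3.5 |

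A Sept-Oct round reproduces the stated 5 and 8 months to about a month. A February round matches neither. Its Survey A ranges from 0.9 months before to 1.9 months after spraying, depending on where in each window the work falls. The table's Jan-Feb questionnaire date could precede a February round altogether.

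**Step 2: keep the intervals instead.** February 2012 + 5 months = July 2012, inside Stage 4. February 2012 + 8 months = October 2012, after Stage 4 ends in August. So neither the printed months nor the printed intervals can be followed in full.

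**Step 3: contrast before the round.** February 2011 to February 2012 is 12 months, with the same planned spray and net history in both arms. Of the 7 monitoring months January to July, 1–2 (1/7 = 14% to 2/7 = 29%) would precede the contrast for EIR and incidence.

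**Step 4: illustration of the direction and possible size.** First reproduce Table 1. Clusters per arm = 1 + (1.645 + 0.842)² × 2v(p)/d², with v(p) = p(1−p)/100 + k²p². For p = 0.04, d = 0.03, k = 0.6:

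- v = 0.000384 + 0.000576 = 0.00096
- clusters = 1 + 6.185 × 0.00192/0.0009 = 14.2, rounded up to the printed 15.

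The same formula reproduces all 14 non-inferiority entries. Table 1 is therefore sized on one survey of 100 per cluster at one-sided 5%.

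Now suppose LLIN alone is truly worse by the full 3-point margin, but only a share of that difference, δ, is visible at Survey A. With 15 clusters per arm and Survey A analysed alone, P(declare non-inferiority) = Φ((0.03 − δ)/SE − 1.645), where SE = √[(v(0.04) + v(0.04 + δ))/15].

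| Share visible (assumed) | δ | SE | P |
|---|---|---|---|
| 0 | 0 | 0.0113 | 0.84 |
| 25% | 0.0075 | 0.0122 | 0.58 |
| 50% | 0.015 | 0.0131 | 0.31 |
| 100% | 0.03 | 0.0150 | 0.05 |

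For three other Table 1 settings at 15 clusters per arm (4%/3 points, 8%/4 points and 10%/5 points, each with k = 0.3), the zero-share figure is 92–97% and the 50%-share figure is 40–48%. The protocol gives no rate at which the arms diverge, so the shares are assumptions.

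**The case against.** The case against has weight on several points.

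- **The surveys are labelled post-intervention and given intervals, and the timetable is marked as changeable.** One could read the opening pronoun of the Stage 4 sentence as covering the whole schedule, so that the surveys would move too. That reading is possible, but the months follow in the very next sentence unadjusted, and the 8-month interval does not fit within Stage 4. An explicit rule is still needed.
- **The harm needs three things together:** the February option, the months kept, and weight placed on Survey A. This is correct. A reader might infer that the design is biased as it stands; it is not, since the expected Sept-Oct round fits the surveys.
- **Combining surveys belongs to the later analysis plan.** Partly so. But when the field survey happens relative to spraying is design, and no analysis restores contrast to a survey already taken.
- **The 84% figure is the least favourable use.** It is the design's power at zero difference, with Survey A deciding alone. A reader might take it as the trial's false-positive rate. The protocol does not make Survey A decisive, so it is not.
- **Calling Survey A a second baseline goes slightly too far.** A small early effect could show by late March.
- **Spray status.** The table's item asks for the share "of households with evidence of IRS in September 2011", which might suggest that a February round would go unrecorded. Section 2.5 requires spray status for each individual in every survey, without a date, so this is a wording matter only.

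**Conclusion.** The point holds as a conditional design weakness. In a branch the protocol itself allows, following the printed months puts Survey A about 0–2 months after the only contrast between the arms, instead of 5. Survey B comes at about 4–5 months (about 2–4 on the table's dates) instead of 8. Any non-inferiority comparison that includes Survey A is then pulled towards success.

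The direction of the bias is certain if LLIN alone is truly worse. Its size is not, because it depends on how fast the arms diverge and how the surveys are weighted, neither of which the protocol gives. The Step 4 figures (84%, 58% and 31% against 5%) mark what could happen if Survey A alone decided; they are not an estimate for the trial. With a Sept-Oct 2011 round the problem does not arise.

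**What to change.** State that survey timing follows the end of the actual arm A round, and align the Stage IV table's dates with the text. If the round is in February 2012:

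- use a Feb-March survey only for baseline adjustment and exclude it from the non-inferiority comparison;
- rest that comparison on the June-July survey, as late as the schedule allows (about 4–5 months);
- count EIR and incidence for the arm comparison only from the end of the round;
- limit the conclusion to the follow-up reached.

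As an editorial change, let the spray-status item refer to the arm A round instead of a fixed month.

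**Cost.** Nothing if spraying is in Sept-Oct 2011. In the February case only one post-intervention survey counts, and there is no 8-month result unless Stage 4 is extended. A July survey also tightens the table's July 2012 laboratory deadlines, the analysis ending in September and dissemination in October. Planned power is kept, because Table 1 was sized on one survey of 100 per cluster.
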